##### II. OTHER MEASURES

###### Residents:

###### - Agitation: CMAI

Cohen-Mansfield Agitation Inventory (CMAI)-Long Form (Cohen-Mansfield, 1986; Cohen-Mansfield, Marx, & Rosental, 1989): Seven-point rating scale (1-never observed to 7-observed a few times in an hour) assessing the frequency with which patients manifest up to 29 behaviours associated with agitation, as observed by care staff over the former two weeks. Inter-rater reliability coefficients are high (0.88 to 0.93) and test/re-test reliability is good ( $r^2=0.74$  to 0.92). (10)

Construct validity of the CMAI Dutch version was established in two independent samples. (48, 49) Factor based symptoms clusters are Physically aggressive, Physically non-aggressive and Verbally agitated behaviour (48). Inter-rater agreement for CMAI items, total score, and cluster scores are 0.22-0.89 (Kappa), 0.89 (Intra Class correlation) and 0.47-0.85 (Inter-rater correlations), respectively. A recent study by the co-applicant [name] shows high inter-rater coefficients of CMAI total and

clusters scores (Spearman's rho 0.82-0.89) and moderate test-retest reliability of CMAI total and cluster scores (Spearman's rho 0.50-0.73). (Submitted)

#### - Other neuropsychiatric symptoms: NPI-NH

The NPI-NH is the only nursing home instrument for assessing neuropsychiatric symptoms that has been translated into Dutch (Kat et al., 2002). The NPI-NH

includes 12 neuropsychiatric symptoms: delusions, hallucinations, agitation, depression, anxiety, euphoria/elation, apathy/indifference, disinhibition, irritability, aberrant motor behavior, nighttime disturbances and appetite/eating change. (50) Both the frequency (F) and severity (S) of each symptom are rated on a four- (1–4) and three-point (1–3) Likert scale, respectively. NPI-NH items test-retest correlations range 0.55-0.88, interrater agreement (Kappa statistic) ranges 0.85-1.00, and between raters correlation range 0.173 to 0.914.

#### - Quality of life - DQoL

Dementia Quality of Life Scale (DQoL) (51) is a 29-item scale which assesses several domains related to quality of life that were identified as important during focus groups held with people with mild and moderate dementia, carers of people with dementia, and health care workers in dementia. Scales (A, B, C): (A) aesthetics (sum scores 5–25); (B) frequency of feelings: B1: positive affect (sum scores 5–30); B2: negative affect (sum scores 5–55); B3: self esteem (sum scores 5–20); B4: feelings of belonging (sum scores 5–15); and (C) overall quality of life (1–5) (higher scores on quality-of-life subscales indicate better quality of life, except for subscale B2). (52)The scale is found to have good internal consistency, reliability and construct validity.(53)

- RCS - Resident Classification Scale (RCS) (54): Standard assessment conducted by RCS-trained staff for all Australian aged/dementia care residents, to determine their care needs and the relative resource allocation required. Overall care/service need is rated from A (very low) to E (very high) and ratings are used to define categories (1–8 categories). Categories 1 and 2 indicate high care needs, and a higher level of funding. The RCS has good concurrent validity with the Modified Barthel Index with high inter- and intra-rater reliabilities (Spearman's  $r^2=0.84$ ).

#### Staff

- Stress reactions. The short version of the General Health Questionnaire (GHQ 12) will be used to measure the staff perceived stress ranging from 0-12 (Koeter and Ormel, 1987; Ormel et al., 1989a; 1989b). Ratings pertain to the weeks preceding the administration of the scale. Answer categories are "absent" (0 points), "the same as usual" (0 points), "more than usual" (1 point), and "a lot more than usual" (1 point).

- Job Satisfaction Maastricht Work Satisfaction Scale for Healthcare (MAS-GZ) by Landeweerd et. Al., 1996) consists of 7 subscales with three items each which are rated on a 5-point scale: satisfaction with quality of care, opportunities for self-actualisation/growth, contact with colleagues, contact with residents, satisfaction with supervisor, possibilities for promotion, and clarity of tasks and rules.

### III. DESCRIPTION DCM-cycle: OBSERVATIONS - FEED-BACK – ACTION PLAN

#### OBSERVATION

In brief, an observer (mapper) observes on average five (4-6) residents with dementia continuously over a representative time period (minimal 4 hours a day) in communal areas (living room) of care facilities. After each 5-min period (a time-frame) the above outlined codes (BCC, WIB) are used to record what has happened to each participant and what the behaviour of the staff was in terms of PDs and PEs. (11, 38)

#### FEED-BACK

In DCM-8, in addition to Personal Detractions (PDs), also the Personal Enhancers (PEs) are been coded, discussed with the staff and related to the residents' ME-values and WIB-scores. Focus group data (11) show that staff appreciated this addition (compared to DCM-7) because they were able to form a complete picture of the participants (residents). Therefore, they were also able to interpret the PD feedback in the context of the lives of participants rather than relating it to themselves in a negative way and possibly becoming defensive. Interestingly, a number of staff teams wanted to keep the strong terminology used in the Personal Detraction coding. Many said that it was this list that had made an impression on them when they first learned about DCM and that it was important not to water this down. This indicates that previously, staff members were possibly not aware of the impact that their behaviour may have on the residents. They seem to appreciate being made aware of this.

#### ACTION PLANS

Based on feedback discussions, staff draws action plans for improving care on an individual and group level. Action plans are 'vehicles' for the implementation of the principles of person centred care (PCC) in daily practice. The standard principles of PCC are:

- Valuing people with dementia and those who care for them (V);
- Treating people as individuals (I);
- Looking at the world from the perspective of the person with dementia (P);
- A positive social environment in which the person living with dementia can experience relative wellbeing (S); (Brooker, 2004, What is person-centred care in dementia? Reviews in Clinical Gerontology 2004 13; 215–222)

In sum, Dementia Care Mapping (DCM) is a method in which care improvement plans ('action plans') are based on systematic observations of the actual care as it takes place in formal settings such as nursing homes and day care. The results are fed-back to the staff, which raises their awareness regarding the dependency between their own behaviour and that of the residents. The feed-back occurs in a non-threatening way and does NOT serve as staff evaluation tool. The fact that not only 'negative' but also positive events are recorded and brought to light motivates staff to improve their competences and performance. DCM offers a set of tools to be used for the purpose of personal, departmental and organizational development. Through DCM, the staff may attain an important signalling role towards the members of the multidisciplinary care teams in nursing homes (psychologists, nursing home physicians, physiotherapists, occupational therapists). This allows for timely initiation of targeted psychological or other interventions. (12) This is very important in ensuring long-term positive effects of DCM. Furthermore, it is important to emphasise that the DCM-method acts as a channel for a timely implementation of various kinds of improvements, from the individual level (resident, caregivers), to group level (residents, caregivers: eg. professional development needs), PGU-level, multidisciplinary team level, management level and organisation level. This way, the improvement actions become sufficiently tailor-made. A large number of studies on effectiveness of psychosocial interventions for people with dementia and their (in)formal caregivers emphasize the need of individually tailored interventions. (55-57)

Dementia Care Mapping method has been extensively used to improve the quality of care in nursing homes. Australian pilot study established decrease in residents Neuropsychiatric Symptoms (CMAI, RMBPC-disruption), as well as improvement in staff interactions with residents with increase in Positive Care, and Positive Social interactions and decrease in Neutral, Negative Protective, and Negative Restrictive interactions. (10) In the first Dutch pilot study positive effects were obtained for patient well being (WIB-scores), anxiety (GIP), agitation (CMAI), positive staff-resident interactions (PEs), and staff satisfaction with contacts with clients (MAS, VAS). (37)

#### IV. IN THE PRESENT STUDY, DCM-INTERVENTION COMPONENTS ARE:

1. Dementia Care Mapping (DCM) Organisational Briefing Day - 1-day training course aimed to provide organization-wide basic understanding of the DCM method thereby ensuring endorsement of DCM goals and methods, and assisting in its implementation into an organization or setting.
2. Staff training-intervention group:
  - Basic user: a 4-day course teaching basic concepts and skills. A basic user can participate in a DCM team under supervision of advanced user;
  - Advanced user: a 3-day course on background and theory of DCM. Advanced user is able to perform care mapping, report observations, lead a DCM-team, give feed-back to the staff and instruct/support them in drawing up action plans. Per organization 1 staff member may become an advanced user while the number of basic users will depend on the number and size of the PGU-units per nursing home.
3. Three DCM-cycles. Description single DCM-cycle: 1. Observing caregiver-patient interactions by the DCM-trained staff over a period of time and recording information about their experience of care; 2. feeding back the results to the staff, 3. staff draw up action plans (in collaboration with other professionals) to bring about changes towards more person-centred care; 4 evaluative observation

#### E. OUTCOME PARAMETERS

- I. Residents: 1. Neuropsychiatric symptoms - primary (CMAI, NPI-NH), 2. Quality of life (WIB, Dqol) – secondary
- II. Staff: 1. Job-related stress – secondary (GHQ – short version); 2. Sense of competence – secondary (SCQ); 3. Job-stress related absenteeism, and turnover (organisational databases) -secondary; 4. Job satisfaction (MAS en VAS) - secondary;

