## Inhoud / Content

### Probleemstelling / Problem definition

#### A. HEALTHCARE PROBLEM:

Prevalence of neuropsychiatric symptoms among nursing home residents with dementia is 83%. (3,19-21) In addition to directly affecting the residents' quality of life, these symptoms represent a serious challenge for the professional caregivers. (13,22) Staff job dissatisfaction brings about high illness absenteeism (5.4%) and turnover rates (brt. 14,1%, net. 6.3%) (23), ultimately leading to staff shortage (41% difficult to fill job openings in 2007). (6, 23-28) A strong relationship found between high employee turnover and poor resident outcomes (6,13, 14) suggests that present effort put into dementia care does not result in sufficient quality and costeffectiveness of care. In order to be able to provide optimal dementia care, staff often needs additional training (4,26,29,30). Except for DCM, no other intervention offers an integral person centred approach to dementia care. Other interventions based on person centred care, such as snoezelen (14,15) and person-centred bathing (31,32) have a more limited scope (residents or staff alone, single psychosocial intervention, or a single caregiving situation). In addition, these interventions often do not include systematic adaptations in management style and organizational climate. It can be expected that all these conditions need to operate synergistically if we are to sustainably improve effectiveness, efficiency and quality of dementia care in nursing homes. We will describe how DCM- intervention fulfils these criteria in the 'Strategy: Intervention' section below. What we hope to achieve is 1. reduction in frequency and intensity of neuropsychiatric symptoms (CMAI, NPI-NH; primary outcome); 2. improvement in quality of life of dementia patients (DCM- WIB, DQoL); 3. improvement in staff-resident interactions, and in staff job satisfaction (DCM: PE/PD, MAS, VAS); 4. reduction in job related stress, absence and staff turnover (GHQ, organisational data bases). In addition we will perform a cost effectiveness analysis in order to find out whether our intervention positively affects the costs of care. Psychometric characteristic of all instruments will be discussed in the section Strategy (Plan van aanpak).

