#### SAMPLE SIZE calculation (motivate assumptions) and feasibility of recruitment

According to a recent RCT-study by Chenoweth et al., (2009), with 5 clusters in the control and 5 in DCM group, 20% attrition rate in 8 months, and an average of 14 evaluable patients at follow up, lead to a treatment difference of 10.9. As the 95% confidence interval of the mean difference was 0.7 - 21.1, the standard error of the difference was approximately  $(21.1 - 0.7) / 4 = 5.1$ .

Therefore, in our study, with similar attrition rate, standard deviation, cluster sizes, ICC, analysis method and design, but with 9 clusters per arm, we would have a standard error of the difference of approximately  $5.1 * \sqrt{5/9} = 3.8$ .

Assuming that the true difference between the treatments is 10.9, the power of our study then is 80% (two-sided testing at  $\alpha=0.05$ ).

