#### F. DATA-ANALYSIS and presentation/syntheses

The effects on the primary outcomes will be evaluated using linear mixed effect models with treatment, baseline measure, and control variables (used in the sequential balancing minimization procedure; Borm et al. 2005) as covariates and Psycho-geriatric unit (PGUU) as a random effect, to correct for dependencies within PGUs. Structural Equation Modeling will be used in the secondary analysis to evaluate the plausibility of a theoretical model of causal chains of effects based on the suggested mediator variables (e.g. WIB, PE/PD). Additionally, quantitative and qualitative process analyses will be carried out in order to determine the level of use of new knowledge and skills in daily practice, and in order to determine relevant facilitators and barriers to implementing new knowledge. To that aim, checklists will be used.

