## I. TIME SCHEDULE: GEDETAILLERDE FASERING

### Months 1-12

1. Symposium with workshops for nursing home staff and managers, and professional organizations in order to acquaint them with the method and raise motivation for their participation in the study;
2. Recruitment and selection of nursing homes, randomisation of eligible PGUs;
3. DCM training (see Intervention components 1 and 2) for organisations and staff

### Months 13 - 24

1. Baseline measurement
2. 4 months DCM-cycle: Observation + Feed-back + Action plan
3. T-1 Measurement
4. 4 months DCM-cycle: Observation + Feed back + Action plan
5. T-2 Measurement

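### CMAI and NPI-NH are both primary and unranked, but the protocol has one alpha of 0.05 and is sized on CMAI alone, so either the error rate or the power of the primary claim is not the stated one

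*Protocol*

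**What the plan says.** Section E. OUTCOME PARAMETERS gives the resident outcome as "Neuropsychiatric symptoms - primary (CMAI, NPI-NH"). The problem definition (A. HEALTHCARE PROBLEM) repeats the pair: "reduction in frequency and intensity of neuropsychiatric symptoms (CMAI, NPI-NH; primary outcome"). The outcome lists in the English and Dutch summaries do the same. None of these places ranks the instruments.

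Section F. DATA-ANALYSIS uses the plural: "The effects on the primary outcomes will be evaluated using linear mixed effect models with treatment, baseline measure", followed by the balancing variables as covariates and the psychogeriatric unit as a random effect. It does not say how results on two primary outcomes combine into one conclusion.

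The sample-size section has one test ("two-sided testing at" 0.05), one treatment difference of 10.9 and one power figure of 80%. The summary identifies 10.90 as a CMAI effect. No treatment effect, standard deviation or power for NPI-NH appears in the Protocol.

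The time schedule lists a baseline, a "T-1 Measurement" after the first four-month cycle and a "T-2 Measurement" after the second. Neither is called the primary time point.

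**The concern.** The design has one alpha and one power figure, and both belong to a single test of CMAI. The primary label covers two instruments. The two can be reconciled only by a rule the Protocol does not give.

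- If a significant result on either instrument answers the primary question, two tests at 0.05 carry a combined error rate above 0.05.
- If both must be significant, the error rate holds, but the power of the claim is that of two tests together. Only one has been sized.
- If alpha is split, the error rate holds, but the CMAI test no longer has the power that was calculated for it.

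The practical risk is a split result, with one instrument significant and the other not. The Protocol then offers no basis for saying whether the primary question was answered.

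**Working it through.** **Inputs from the Protocol.** Difference 10.9; 95% confidence interval in the source trial 0.7 to 21.1 with 5 clusters per arm; 9 clusters per arm planned; two-sided alpha 0.05; stated power 80% (sample-size section). The identification with CMAI comes from the summary. The summary labels 3.8 as an SD, but the sample-size section derives it as the standard error of the difference, and it is used that way here.

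**1. Reproducing the stated power.**
- Standard error with 5 per arm: (21.1 - 0.7)/4 = 5.1.
- Standard error with 9 per arm: 5.1 × √(5/9) = 3.80.
- Power = Φ(10.9/3.8 - 1.960) = Φ(2.868 - 1.960) = Φ(0.908) = 81.8%.

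This agrees with the stated 80%. A t reference with 16 degrees of freedom (18 clusters minus 2) gives 76.8%. Either way the figure is for one CMAI test at 0.05.

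**2. Either instrument is enough.** The chance of at least one false positive is P(|Z1| > 1.96 or |Z2| > 1.96) when neither instrument has an effect. Under independence this is 1 - 0.95² = 9.75%, and in the favourable direction only it is 1 - 0.975² = 4.9%. For correlated statistics it was simulated from a bivariate normal distribution (2 million draws). The Protocol gives no correlation between the two tests, so the values below are assumptions.

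| Assumed correlation | Any false positive, two-sided | Favourable direction only |
|---|---|---|
| 0 | 9.75% | 4.9% |
| 0.3 | 9.5% | 4.8% |
| 0.5 | 9.1% | 4.5% |
| 0.7 | 8.4% | 4.2% |
| One test, for comparison | 5% | 2.5% |

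**3. Alpha split equally (0.025 each).** CMAI power = Φ(2.868 - 2.241) = Φ(0.627) = 73.5% with 9 clusters per arm (65.5% with t on 16 degrees of freedom). Returning to 80% takes 11 clusters per arm: 5.1 × √(5/11) = 3.44, and Φ(10.9/3.44 - 2.241) is about 82%. The t version needs 12. The Protocol plans 18 to 20 units in all, which is 9 to 10 per arm.

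**4. Both must be significant.** The error rate does not exceed 0.05. Joint power cannot exceed the CMAI power of 81.8%, and its value cannot be computed without an NPI-NH effect and standard deviation. As an illustration only, if NPI-NH happened to have the same power and the tests were independent, it would be 0.818² = 66.9%.

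**The case against.** The strongest reply is that the Protocol states no success rule, so it cannot be said to allow a win on either instrument. If both were meant to be required, alpha is not inflated. A separate statistical analysis plan might also add a multiplicity rule. This stands in part: an inflated error rate is one possible consequence, not something the plan declares. It does not remove the point, because the designation of two primaries and the sizing on one are fixed in the Protocol. A later rule could protect alpha, but it could not make the 80% apply to a claim that rests on both instruments or on a split alpha.

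A second fair objection concerns the percentages. The research question is about reducing symptoms, so a significant result in the harmful direction would not count as success. That is correct, and the favourable-direction column is the figure for a false claim of benefit. The relative increase is much the same: 4.2-4.9% against 2.5%.

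A reader might go further and infer four routes to success: two instruments at each of two follow-ups. The documents do not support that. The schedule says when measurements are taken and not what is tested. The analysis section names one treatment term and no separate test per visit. The eight-month attrition used for sizing matches two four-month cycles and so points to T-2. Choosing the visit and modelling repeated measures are also commonly left to an analysis plan.

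**Conclusion.** The point holds for the two instruments. The Protocol names two unranked primary outcomes, sets one two-sided alpha of 0.05 and sizes the trial on CMAI only. The consequence depends on the unstated rule:

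- either instrument: a two-sided error rate of about 8.4-9.5% (9.75% at most, under independence), or roughly 4-5% against 2.5% for false claims of benefit;
- both instruments: a power that is not the stated 80%, cannot exceed the CMAI power, and cannot be computed from the Protocol;
- a Bonferroni split: CMAI power of about 73.5% with 9 clusters per arm.

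The error rates rest on assumed correlations of 0.3 to 0.7. The power figures rest on the Protocol's own difference and standard error. It does not follow that the plan grants success on either instrument or at either visit, because it states neither. This should be settled before analysis. It does not call the design or the data collection into question.

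**What to change.** In section E. OUTCOME PARAMETERS, in A. HEALTHCARE PROBLEM and in the summary outcome list:

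- name the CMAI total score as the single primary outcome, tested once at two-sided 0.05, with T-2 (the eight-month horizon behind the sizing) as the primary time point;
- make NPI-NH the first key secondary outcome, tested only if CMAI is significant;
- treat T-1 as secondary.

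Bring the Dutch summary and the plural in section F. DATA-ANALYSIS into line. The sizing refers to CMAI without saying total or cluster score, so the sponsor should confirm that 10.9 is a total-score difference.

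The cost is wording only: no new data, no more units, and the basis of the stated power is unchanged. The downside is that NPI-NH loses its primary label. If the sponsor wishes to keep both as primary, a written rule is needed with sizing to match. An equal alpha split needs 11 clusters per arm by the Protocol's own formula. A both-must-succeed rule needs an NPI-NH effect and standard deviation before its power can be stated.

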#### SAMPLE SIZE calculation (motivate assumptions) and feasibility of recruitment

According to a recent RCT-study by Chenoweth et al., (2009), with 5 clusters in the control and 5 in DCM group, 20% attrition rate in 8 months, and an average of 14 evaluable patients at follow up, lead to a treatment difference of 10.9. As the 95% confidence interval of the mean difference was 0.7 - 21.1, the standard error of the difference was approximately  $(21.1 - 0.7) / 4 = 5.1$ .

Therefore, in our study, with similar attrition rate, standard deviation, cluster sizes, ICC, analysis method and design, but with 9 clusters per arm, we would have a standard error of the difference of approximately  $5.1 * \sqrt{5/9} = 3.8$ .

Assuming that the true difference between the treatments is 10.9, the power of our study then is 80% (two-sided testing at  $\alpha=0.05$ ).

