#### STUDY POPULATION(S)/datasets:

280 nursing home residents with dementia and one or more neuropsychiatric symptoms, and their professional caregivers from 18-20 PGUs in the Netherlands.

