#### SAMPLE SIZE CALCULATION/DATA ANALYSIS

- power- 80%
- effect size 10.90 (SD=3.8) on CMAI(10),
- ICC - 0.05,
- cluster size - 14 observations,
- alpha - .05,
- 20% attrition rate per 8 months
- sample size - N=260-280 or 18-20 PGUs.

The effects on the primary outcomes will be evaluated using linear mixed effect model.

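### The enrolment target of 260–280 residents does not allow for the 20% attrition that the standard error of 3.8 presupposes has already happened

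*Protocol*

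**What the plan says.** The Protocol section on sample size and feasibility of recruitment builds its precision on one published cluster trial, "with 5 clusters in the control and 5 in DCM group" and "20% attrition rate in 8 months, and an average of 14 evaluable patients at follow up". It turns that trial's interval into a standard error ("As the 95% confidence interval of the mean difference was 0.7 - 21.1", hence 5.1). It then multiplies by √(5/9) for 9 units per arm, on the assumption that attrition, standard deviation, cluster sizes and ICC are similar. The result is an SE of 3.8. "Assuming that the true difference between the treatments is 10.9", the section concludes that "the power of our study then is 80% (two-sided testing at" the 5% level.

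The English summary lists a cluster size of 14 observations, an ICC of 0.05, 20% attrition per 8 months, and "sample size - N=260-280 or 18-20 PGUs". The Dutch summary repeats these figures. The summary's study-population entry reads "280 nursing home residents with dementia and one or more neuropsychiatric symptoms", and section C of the Strategy chapter (study population) also gives 280 patients, directly above the recruitment plan and the inclusion criteria.

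**The concern.** The SE of 3.8 holds only if each psycho-geriatric unit (PGU) still has 14 residents with data at follow-up. The stated total is about 14 per PGU at entry. The 20% loss appears among the inputs, but no step turns an evaluable number into a number to enrol.

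Two things are at stake. The precision quoted for the primary CMAI comparison may be better than the planned enrolment can give. And a site that takes 14 as its recruitment target would end with about 11 evaluable residents (14 × 0.8 = 11.2).

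**Working it through.** **Inputs.** From the sample-size section: difference 10.9, source interval 0.7 to 21.1, 5 clusters per arm in the source trial, 14 evaluable per cluster, 9 clusters per arm planned, two-sided 5% level. From the summary: ICC 0.05, attrition 20%, N = 260–280, 18–20 PGUs.

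**Step 1: the plan's own figures.**
- Source SE = (21.1 − 0.7)/4 = 5.10.
- Planned SE = 5.10 × √(5/9) = 3.80.
- Power = Φ(10.9/3.80 − 1.96) = 81.8%. With a divisor of 3.92 instead of 4, the SE is 3.88 and power 80.2%.

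The stated 80% is reproduced, for 14 evaluable residents in each of 18 PGUs.

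**Step 2: where N comes from.** 18 × 14 = 252 and 20 × 14 = 280. The upper end of the range is exactly PGUs times 14, and the lower end is 8 residents above 252. The range exceeds 252 by 3% to 11% (260/252 and 280/252), whereas a 20% loss calls for 25% more (1/0.8).

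**Step 3: enrolment that matches SE 3.8.** 252/0.8 = 315 residents in 18 PGUs, or 17.5 per PGU. Against 260–280 that is a gap of 35–55 residents at 18 PGUs.

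**Step 4: precision if 260–280 are enrolled.** Evaluable residents number 260 × 0.8 = 208 to 280 × 0.8 = 224. With k PGUs per arm and m evaluable residents per PGU,

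SE = 5.10 × √(5/k) × √[f(m)/f(14)], where f(m) = [1 + (m − 1) × 0.05]/m and f(14) = 1.65/14 = 0.1179.

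Power = Φ(10.9/SE − 1.96).

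| Enrolled / PGUs | m | f(m) | SE | Power |
|---|---|---|---|---|
| 260 / 18 | 11.6 | 0.1322 | 4.03 | 77.3% |
| 280 / 18 | 12.4 | 0.1263 | 3.94 | 79.1% |
| 260 / 20 | 10.4 | 0.1413 | 3.95 | 78.8% |
| 280 / 20 | 11.2 | 0.1348 | 3.86 | 80.7% |
| 315 / 18 | 14.0 | 0.1179 | 3.80 | 81.8% |

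None of the four combinations from the stated range reaches SE 3.80. Three of them fall 1 to 3 points below 80% power, and 280 in 20 PGUs stays above it.

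**Step 5: sensitivity to the ICC.** Values other than 0.05 are assumptions, anchored to the same source SE. For 280 in 20 PGUs, power is 77.1% at ICC 0, 78.2% at 0.01 and 82.3% at 0.10. A smaller ICC makes the lost residents matter more.

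**The case against.** The best defence is that attrition is already inside the calculation. The SE was borrowed from a trial that had lost 20%, and the section expressly carries over similar attrition and cluster sizes. That covers the evaluable count but not enrolment: to finish with 14 per PGU, a 20% loss means starting with 17 or 18.

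The 280 might instead be read as evaluable residents. The study-population section favours the other reading, since it describes the people to be recruited. If 280 were evaluable, the protocol would give no enrolment target at all.

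The step from 18 to 20 PGUs might be the allowance, and the closing summary of changes does say that somewhat lower drop-out helped to keep the sample size unchanged. Neither place presents the two extra PGUs as cover for attrition, and the range still admits 18. What stands is that 280 in 20 PGUs does keep power at about 81%.

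Three stronger readings are not supported:

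- A reader might infer that 80% power is missed throughout. It is not, as the 280-in-20 case shows.
- A reader might add a t reference on 16–18 degrees of freedom and quote 72–76% power, or a detectable difference of 11.4–12.0 points. Most of that drop comes from the reference distribution and not from attrition. It also depends on how the source interval was computed, which the protocol does not say. If that interval used t on 8 degrees of freedom, the source SE is 20.4/(2 × 2.306) = 4.42, and t-based power after the 20% loss is 83–87% over the same four combinations.
- A reader might say that the summary and the sample-size section contradict each other on the meaning of 14. The summary says observations, which is compatible with evaluable residents. The term is unlabelled, not contradictory.

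**Conclusion.** The point holds in a limited form. The SE of 3.8 and the 80% power rest on 14 evaluable residents per PGU, while the stated study population is about 14 per PGU before attrition. Reading 260–280 as enrolled, with 20% loss, ICC 0.05, a source SE of 5.1 and the protocol's normal approximation, the SE is 3.86–4.03 instead of 3.80. Power is about 77–79%, or about 81% at 280 residents in 20 PGUs.

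The stated precision is therefore missed across the range, but the cost in power is at most about 3 points below 80% and depends on the number of PGUs. This is a stated figure that should be corrected. It does not undermine the design. The gap of 35–55 residents against SE 3.8 in 18 PGUs depends only on the 20% loss and the 14 evaluable per PGU, not on the ICC or the reference distribution.

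**What to change.** In the sample-size section and both summaries:

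- Label 14 as evaluable residents per PGU at follow-up.
- State the enrolled and evaluable numbers separately: 260–280 enrolled and 208–224 evaluable after 20% attrition.
- Keeping 260–280 enrolled, restate the SE as about 3.9–4.0 and power as about 77–81%, and say which number of PGUs each figure belongs to.

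This needs no extra residents or PGUs. It costs a few lines of text and a slightly lower stated power for most of the range. If the sponsor prefers to keep SE 3.8 with 18 PGUs, the matching enrolment is about 315 residents, 17–18 per PGU, which means 35–55 more to recruit.
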